## Abstract

**Background:**

Despite a steady world-wide decline over recent decades, rates of smoking remain high in developed countries. In Japan, 30% of men and 10% of women are smokers. Based on these rates, 18.8 million (14.06 million men and 4.74 million women) in Japan are smokers. The rate of success for smoking cessation has recently improved due to the widespread availability of drug therapy; however, the success rate for quitting smoking one year after beginning therapy is only around 50%. Previous studies have demonstrated that exercise can relieve mental stress during continuous abstinence from smoking and curb smoking resumption. To date, no large-scale, randomized controlled trials have examined the effects of exercise on smoking cessation. The present study aims to determine the effects of exercise instruction on continuous abstinence from smoking after completion of smoking cessation therapy.

**Methods:**

This is a multicenter, prospective, parallel-group, randomized controlled trial in Japan. We will enroll 300 individuals visiting a smoking cessation clinic (over 3 months) who have abstained from smoking in the second month after their initial visit as potential participants. Participants will not habitually exercise and will need to consent to participate. Participants will be randomly assigned to the exercise intervention group or control group. The intervention group will receive instruction on exercises that can be incorporated into their daily lives. The control group will be followed during the standard smoking cessation support program. The primary endpoint will be the continuous abstinence rate, and secondary endpoints will be weight, blood pressure, exhaled carbon monoxide concentration, psychological state, and blood test results. These indices will be compared between the intervention and control groups, with follow-up periods of 9 months in both groups.

**Discussion:**

By examining the effects of exercise instruction after completion of 12-week smoking cessation therapy, this study should yield quality information that can be used to develop protocols to improve the continuous abstinence rate and inhibit weight gain after smoking cessation therapy.

**Trial registration:**

UMIN Clinical Trials Registry, UMIN000014615. Registered on 1 October 2014.

## Background

### Smoking is a major health issue in Japan

Smoking is a major health issue that is associated with the development of malignancies, respiratory diseases, and cardiovascular diseases such as cerebrovascular disease and ischemic heart disease. The Japan Collaborative Cohort Study of 95,000 Japanese participants indicated that smoking increases the risk of death due to cardiovascular disease 1.6–2.0-fold. Moreover, numerous Japanese cohort studies have reported that the population attributable risk of cardiovascular disease due to smoking is approximately 20% for men and > 5% for women [1]. In Japan, the current rate of smoking is 30% in men and 10% in women. Despite a steady decline over the last few decades, smoking rates remain high in developed countries [2]. In Japan, > 1 million people suffer from smoking-related conditions such as malignancies, cerebrovascular diseases, or cardiovascular diseases, and the medical expenses attributed to smoking (and passive smoking) are estimated to be as high as 1.49 trillion Yen [3].

### Quitting smoking promotes public health

Quitting smoking has numerous preventive effects, such as an improved prognosis for avoidance of cardiovascular disease [4]. Furthermore, symptoms of chronic bronchitis improve 1–2 months after smoking cessation; patients with mild-to-moderate chronic obstructive pulmonary disease have improved pulmonary function 1 year after quitting smoking; risk of coronary artery disease decreases within 2–4 years; patients with a history of coronary artery disease have a 35% lower risk of recurrence or death; and former smokers have a rate of diminished pulmonary function equivalent to that of nonsmokers after 5 years. Moreover, individuals aged 40–59 years who attempt to quit smoking have a significantly lower risk of incurring massive medical expenses in the future compared with continuing smokers, and individuals attempting to quit smoking have a reduced risk of massive medical expenses similar to that of lifetime nonsmokers [5]. Thus, actively promoting smoking cessation should significantly inhibit the development of cardiovascular disease and greatly reduce medical expenses.

### Smoking cessation aids lack sufficient long-term effectiveness

Many people smoke again within 1 year after the initial consultation at the smoking cessation clinic, even if they quit smoking successfully. However, if they could continue quitting smoking for more than 1 year, fewer people would smoke again. Since the term of the smoking cessation therapy at clinics in Japan is 3 months, it is necessary to follow up for the remaining 9 months after the 3-month therapy (total of 1 year). In April 2006, Japanese national health insurance started to include smoking cessation treatment, and covers treatment for 3 months. The rate of success for individuals quitting smoking has recently improved due to the widespread availability of drug therapy at smoking cessation clinics. Since its introduction to the Japanese market in 2008, varenicline tartrate, an oral smoking cessation aid, has increased the success rate of smoking cessation treatment immediately after completion to approximately 70%. However, the continuous abstinence rate drops to approximately 50% 1 year after start of therapy [6]. This highlights the urgent requirement for medical personnel to provide support to individuals attempting to quit smoking to help them avoid resuming the habit.

### Exercise can improve the rate of quitting smoking

Exercise can relieve mental stress, during continuous abstinence from smoking, and curb smoking resumption [7]. A systematic review of the efficacy of exercise showed that it helped to curb smoking resumption in 12 out of 14 studies [8]. Similarly, a meta-analysis also indicated that exercise, as part of a cardiac rehabilitation program, significantly reduced the smoking rate [9]. Active incorporation of exercise may improve the rate of quitting smoking.

### Exercise can inhibit weight gain after quitting smoking

Weight gain typically occurs after smoking cessation. A recent meta-analysis reported that people on average gain 4.7 kg in weight 1 year after quitting smoking [10]. Weight gain after smoking cessation may lead to the resumption of smoking, and preventing weight gain is a vital aspect of smoking cessation support. Japanese smoking cessation programs using drug therapy provide instruction primarily in the form of diet and cognitive behavioral therapy; however, several studies have reported that such programs may not result in adequate weight control [11, 12]. Explaining specific forms of exercise to individuals who are attempting to quit smoking and do not exercise may help to improve the success rate for quitting smoking and help manage subsequent weight control.

Several intervention studies have examined the effects of combining exercise instruction with drug therapy. In a systematic review of 20 studies (including 5870 participants) examining the effectiveness of exercise interventions, the largest of the 20 studies was an Internet trial of 2318 individuals. Of the 20 studies, 8 had fewer than 30 subjects, 9 included only women, and 1 included only men. Although 4 of 20 studies reported adequate sample size and the effectiveness of exercise in smoking cessation, the effect of exercise instruction on smoking cessation remains unclear [13].

## Study objective

The present study aims to determine the effects on continuous abstinence from smoking of exercise instruction provided after completion of 12-week smoking cessation therapy (covered by the national health insurance).

## Methods/design

### Study design

This will be a multicenter intervention study with centralized enrollment (open-label, prospective, parallel-group, randomized controlled trial). Three institutions participated in this study (Kyoto Medical Center, Kumamoto Red Cross Hospital, and Komoro Kosei Hospital). Two of the facilities are located on the west side of Japan and one on the east side.

### Sample size

Previous research has shown that the addition of exercise instruction increased the odds ratio of successful smoking cessation threefold after 6 months. Of the 306 people screened by phone in this study, 40 people were considered eligible and gave consent to participate. After the 2-week run-in period, 26 individuals were randomized to the intervention and control groups, including 13 women and 12 men (excluding 1 participant who developed lung cancer) [14]. Assuming that the addition of exercise instruction after the anticipated conclusion of drug therapy is estimated to increase the odds ratio twofold after 9 months, and the standard therapy group is estimated to successfully quit smoking at a rate of 50%, then for power of 1−β = 0.8 and type I error of α = 0.05 the minimum sample size required would be 134 participants per group, making a total of 268 participants. Assuming a dropout rate of 10% during the study, a randomized intervention study with 150 participants per group will require a total of 300 participants [15]. Study participants will be allocated to one of two groups: an exercise intervention group, who will receive additional exercise instruction in addition to the standard instruction, and a control group, who will receive the standard instruction. Participants will be followed for 9 months after enrollment. The target number of participants to be enrolled is 300 (150 in each group).

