### Inclusion criteria

Individuals who have abstained from smoking during the last month while undergoing standard smoking cessation therapy (3 months after the initial visit) and fulfilling the following will be included: (1) individuals who do not exercise (those who do not answer “I have continued to exercise 30 min a day at least twice a week for over a year” in a questionnaire); (2) age 20–75 years; and (3) individuals who agree to the purpose of this study and who provide written consent.

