#### Items analyzed and analytical methods

The characteristics of the participants in both groups will be described statistically. Changes in the metabolic index and psychological state from enrollment to 9 months after enrollment will be compared between the two groups. The distribution of individual indices at baseline and 9 months after enrollment will be determined in the two groups, and the *t* test or a Wilcoxon rank-sum test will be performed. Analysis of covariance, multiple regression, or logistic regression will be used for factor adjustment. In addition, Fisher’s exact test will be used to compare the continuous abstinence rate in the two groups. The level of significance will be *p* ≤ 0.05. Two-tailed alpha of 5% and two-sided 95% confidence level will be used. A statistician will perform the statistical analysis.

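### The 50% control rate belongs to all smokers who start therapy; the trial enrols only those abstinent at its end, for whom the protocol's own figures imply about 71%, so the stated 80% power is not delivered

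*Protocol article*

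**What the plan says.** All references are to the protocol article.

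- **Sample size.** The control assumption is that "the standard therapy group is estimated to successfully quit smoking at a rate of 50" per cent. The intervention "is estimated to increase the odds ratio twofold after 9 months". The calculation is done "for power of 1−β = 0.8 and type I error of α = 0.05", and "the minimum sample size required would be 134 participants per group, making a total of 268 participants". Allowing for 10% dropout, the target is 150 per group, 300 in all. No source is given for the 50%.
- **Background, on the long-term effectiveness of cessation aids.** Varenicline "has increased the success rate of smoking cessation treatment immediately after completion to approximately 70" per cent, but "the continuous abstinence rate drops to approximately 50% 1 year after start of therapy". The abstract also counts its 50% from the beginning of therapy.
- **Inclusion criteria.** "Individuals who have abstained from smoking during the last month while undergoing standard smoking cessation therapy (3 months after the initial visit") may enter. Follow-up is nine months from enrolment, that is, to about one year from the start of therapy.
- **Analysis set.** The abstinence rate uses every participant in the group as its denominator.
- **Items analyzed and analytical methods.** Fisher's exact test compares the abstinence rates, and "Two-tailed alpha of 5% and two-sided 95% confidence level will be used".

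**The concern.** The 50% in the sample size section equals the Background figure for one year after starting therapy. That figure includes smokers who had not stopped by the end of therapy, and none of them can enter this trial. Among those who can enter, the rate at the same time point must be higher.

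This matters because the plan fixes an odds ratio, not an absolute difference. At a fixed odds ratio of 2, a control rate above 50% shrinks the absolute difference and raises the required sample size. A trial believed to have 80% power would then miss a true odds ratio of 2 far more often than one time in five, and a null result could be misread as good evidence of no effect.

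**Working it through.** **Inputs.** From the sample size section: control 50%, odds ratio 2, power 0.80, alpha 0.05, 134 evaluable and 150 enrolled per group. Two-sided testing and Fisher's test come from the analysis methods. The 70% at end of therapy and 50% at one year come from the Background.

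**1. Reproducing the plan's figure.** Odds at 50% are 1; doubled they are 2, so the intervention rate is 2/3 = 66.7%. With unpooled variances,

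n = (1.960 + 0.842)² × [p₁(1−p₁) + p₂(1−p₂)] / (p₂−p₁)²
= 7.849 × (0.2500 + 0.2222) / 0.1667² = 133.4, rounded up to 134.

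This matches. 134/0.90 = 148.9, so 149, rounded to 150. The arithmetic is sound; only the control-rate input is in question.

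**2. Control rate for the enrolled population.** Anyone continuously abstinent at one year was abstinent at three months, so

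P(abstinent at 1 year | abstinent at 3 months) = 0.50/0.70 = 0.714.

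**3. Intervention rate at the plan's odds ratio.** Odds are 0.714/0.286 = 2.5; doubled, 5; so 5/6 = 83.3%. The difference is 11.9 points instead of 16.7.

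**4. Required size by the same formula.**

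n = 7.849 × (0.2041 + 0.1389) / 0.1190² = 190 per group

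(193 with pooled variance under the null).

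**5. Exact power at odds ratio 2**, by enumerating all outcomes of two binomials:

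| Control rate | 134/group: chi-square | 134/group: Fisher | 150/group: chi-square | 150/group: Fisher |
|---|---|---|---|---|
| 50% (plan) | 80.4% | 76.8% | 84.4% | 81.4% |
| 60% | 74.9% | 70.8% | 79.6% | 76.1% |
| 65% | 71.6% | 66.6% | 76.2% | 72.3% |
| **71.4%** | **65.2%** | **59.2%** | **69.9%** | **65.1%** |
| 75% | 60.5% | 54.3% | 65.3% | 59.7% |
| 80% | 52.2% | 46.1% | 56.9% | 50.7% |

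The first row separates two effects. At 134 per group, using Fisher's test costs about 4 points even at the plan's own rates (80.4% to 76.8%). The control rate costs a further 18 points under Fisher (76.8% to 59.2%), or 15 under chi-square (80.4% to 65.2%).

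**6. Odds ratio detectable with 80% power at a 71.4% control rate:** 2.33 (chi-square) or 2.46 (Fisher) with 134 per group; 2.21 or 2.31 with 150.

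**7. Dropouts counted as smokers** (an assumption; 10% in each arm). Rates become 0.9 × 71.4% = 64.3% and 0.9 × 83.3% = 75.0%. Power with 150 per group is 53% (chi-square) or 48% (Fisher).

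**The case against.** **The 71% is inferred, not stated.** The sample size section gives no source for its 50%, and the denominators of the Background figures rest on a cited source not at hand. If that 50% were a rate among people who had already quit, the plan would be right. However, the Background presents a success rate of about 70% that falls to about 50%, and dates the second figure from the start of therapy. The natural reading is one denominator for both, and the document offers no other basis for 50%. What stands is that both inputs are approximate: 50/75 would give 67% and 45/70 would give 64%.

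**The subset step depends on how abstinence was defined.** If the one-year figure meant only recent abstinence, some of the 50% could have been smoking at three months, and 50/70 would be too high. For the conditional rate to fall to 60%, 8 of every 50 one-year abstainers would have to come from the 30% who had failed at three months (0.60 × 70 = 42). Power at 134 per group would still be 75% (chi-square) or 71% (Fisher). The enrolled non-exercisers may also differ from clinic attendees in general.

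**The analysis set is intention-to-treat, so 150 is the relevant number.** At 150 per group and a 60% control rate, chi-square power is 79.6%, essentially the stated figure. This stands for the low end of the range under chi-square, but Fisher gives 76.1% there. Keeping all 150 in the denominator also means deciding how dropouts count, and counting them as smokers lowers power further.

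**A 50% rate is conservative.** That holds when an absolute difference is fixed. At a fixed odds ratio of 2 the same formula is smallest near a 41% control rate (about 130 per group), so 50% is close to the most favourable choice.

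**The loss depends on holding the odds ratio at 2.** This stands. Keeping the 16.7-point difference instead (71.4% v 88.1%) would give about 93% power at 134 per group, but it needs an odds ratio of about 3, which the plan does not assume for this trial.

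**Conclusion.** The concern holds. The calculation is done correctly on a control rate that belongs to a different population. On the protocol's own figures the rate among those enrolled is about 71%. At the protocol's odds ratio of 2, power is then about 65% (59% with Fisher) with 134 evaluable per group, or 70% (65%) if all 150 are evaluable. The chance of missing such an effect at 134 per group is about 35% to 41%, not 20%.

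The conclusion rests on three assumptions: the 70% and 50% share a denominator; one-year abstainers are a subset of end-of-therapy abstainers; and the odds ratio stays at 2. The exact 71% is uncertain, but the direction is robust: every control rate from 60% to 80% falls short of 80% power, only marginally so at 60% with all 150 per group under chi-square. There is no bias and no inflation of type I error. The fault lies in a stated design property that the trial does not have.

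**What to change.** In the sample size section:

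1. Replace the 50% with a control rate conditional on abstinence at enrolment, about 71%. Show its derivation from the 70% and 50% in the Background, and label it approximate.
2. Restate what 300 participants deliver at an odds ratio of 2: about 65% power (59% with Fisher) with 134 evaluable per group after 10% dropout, and 70% (65%) if all 150 are evaluable. Equivalently, after dropout there is 80% power for an odds ratio of about 2.3 (chi-square) to 2.5 (Fisher).
3. Give a short sensitivity range, for example control rates of 60% to 80%, and say how dropouts are counted in the denominator.

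A covariate-adjusted primary analysis, using the logistic regression the plan already mentions and the allocation factors, may recover some power. The gain is not quantified here and should not be assumed.

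The cost is one reworded paragraph and a less favourable stated power. No extra enrolment is asked for. Recruitment was still open when the article was submitted; the change should be made before outcomes by group are known.

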### Analysis

#### Analysis set

The two groups (exercise intervention and control groups) will be compared based on the intention-to-treat principle. All data for the metabolic indices and psychological states of the participants in each group obtained upon enrollment and 9 months after enrollment will be analyzed. Individuals who quit smoking for a prolonged period will be similarly analyzed and those who resume smoking will be excluded. Quitting smoking for a prolonged period is defined as not smoking for 9 months after enrolling in the study (determined by interview) and having exhaled carbon monoxide levels ≤ 7 ppm. The continuous abstinence rate is defined as the proportion of participants who abstain from smoking with respect to the total number of participants in each group.

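### The 134 per group for 80% power belongs to an uncorrected normal approximation, not to the planned Fisher's exact test, and the 10% dropout allowance does not fit a denominator of everyone randomised

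*Protocol article*

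**What the plan says.** The Sample size section of the protocol article assumes that "the standard therapy group is estimated to successfully quit smoking at a rate of 50" per cent and that adding exercise instruction "is estimated to increase the odds ratio twofold after 9 months". The resulting figure is that "the minimum sample size required would be 134 participants per group, making a total of 268 participants". The error rates behind it are a power of 0.8 and an alpha of 0.05. Next comes "Assuming a dropout rate of 10% during the study", which leads to 150 per group and 300 in total. The section does not name the test or formula, and it does not say whether the 50% is a rate among those who complete follow-up or among everyone randomised.

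Three other sections bear on the figure:

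- **Items analyzed and analytical methods** fixes the primary comparison: Fisher's "exact test will be used to compare the continuous abstinence rate in the two groups". It also fixes the sidedness: "Two-tailed alpha of 5% and two-sided 95% confidence level will be used".
- **Analysis set** applies the intention-to-treat principle and defines the continuous abstinence rate as "the proportion of participants who abstain from smoking with respect to the total number of participants in each group".
- **Items observed and studied**, like Analysis set, accepts a participant as abstinent only on an interview report together with exhaled carbon monoxide of 7 ppm or less.

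**The concern.** A stated power is a property of a particular test applied to a particular analysis set. Here the test behind the 134 is not the planned test, and the treatment of dropouts behind the 150 is not the one that the endpoint definition implies. Fisher's test is conservative at these sizes, so a number that just reaches 80% under an uncorrected approximation falls short under Fisher. Dividing by 0.9 restores a headcount of completers. It does not restore a difference that shrinks when losses stay in the denominator without being able to qualify as abstinent.

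At stake is how a non-significant result would be read. If true power is 72% and not 80%, the chance of missing the assumed effect is 28% and not 20%.

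**Working it through.** **Inputs.** Control rate p1 = 0.50, odds ratio 2, power 0.80, alpha 0.05, dropout 10% and 150 per group are from Sample size. The two-sided test and Fisher's exact test are from Items analyzed and analytical methods. The denominator is from Analysis set.

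**Intervention rate.** The control odds are 0.5/0.5 = 1. Doubled they are 2, so p2 = 2/3 = 66.7%. The difference is 1/6, or 16.7 points.

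**Reproducing the 134.** Unpooled normal approximation, no continuity correction:

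n = (z(0.975) + z(0.80))² × [p1(1 − p1) + p2(1 − p2)] / (p2 − p1)²

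= 7.849 × (0.2500 + 0.2222) / 0.02778 = 133.4, rounded up to **134**.

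Then 134/0.9 = 148.9, so 149, rounded to 150. The plan's figures are therefore a correct calculation for that formula. Two common variants give 137 (pooled variance) and 148 (continuity-corrected, which is close to Fisher).

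**Power of the planned test.** For each n, every pair of outcomes of two binomials was enumerated, and the probabilities of those with a two-sided Fisher p-value of 0.05 or less were summed. At 50% v 66.7%:

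| Analysed per group | Fisher's exact | Uncorrected chi-square |
|---|---|---|
| 134 | 76.7% | 80.4% |
| 135 (150 less 10%) | 76.8% | 80.3% |
| 146 | 79.6% | – |
| 147 | 80.0% | – |
| 150 | 81.4% | 84.4% |

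Fisher first reaches 80% at 147 evaluable per group. With the plan's own allowance that is 147/0.9 = 163.3, so 164 enrolled per group, against 150 planned.

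**Effect of the denominator.** Suppose 50% and 66.7% are rates among completers, 10% are lost in each arm, and a lost participant cannot meet the interview-plus-carbon-monoxide definition. The rates over all randomised are then:

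- control: 0.9 × 50% = 45%
- intervention: 0.9 × 66.7% = 60%

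The difference falls from 16.7 to 15 points, and the odds ratio to (0.60/0.40)/(0.45/0.55) = 1.83. At 150 per group, Fisher has 72.1% power and an uncorrected chi-square test 75.9%. Fisher would need about 183 per group. With smaller losses counted the same way, Fisher power at 150 is 79.6% at 2% loss and 76.9% at 5%.

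**Summary for Fisher's test with 150 enrolled per group:**

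| Reading of the 50% and the dropouts | Rates compared | Analysed per group | Power |
|---|---|---|---|
| Completer rates, dropouts left out | 50% v 66.7% | 135 | 76.8% |
| Completer rates, dropouts count as not abstinent | 45% v 60% | 150 | 72.1% |
| Rates already count losses as failures | 50% v 66.7% | 150 | 81.4% |

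**The case against.** The strongest reply is that the trial as enrolled may be adequately powered. If 50% and 66.7% are rates over everyone randomised, Fisher's test on 150 per group gives 81.4%. The Background section uses the term continuous abstinence rate for its figure of about 50% at one year, and Analysis set defines that same term over all participants. This stands, and it is why no single power figure can be asserted. But Sample size does not describe its rates that way. On that reading a dropout allowance has no purpose, whereas the section moves from 134 to 150 precisely by allowing for dropout.

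Second, 72.1% rests on an effect smaller than the plan's odds ratio of 2. If the control rate were 45% and the odds ratio stayed at 2 (45% v 62.1%), Fisher at 150 would have 83.0%. That is correct arithmetic, but it requires the odds ratio of 2 to hold over all randomised. It is again a question of which population the assumptions describe.

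Third, no sentence says outright that a lost participant counts as a smoker, and handling of missing outcomes may be set out in a document not shown. This also stands. The rule is inferred from the denominator and the two-part definition of abstinence. Analysis set does exclude those who resume smoking, but that sentence follows the metabolic and psychological analyses. It cannot govern the primary rate, which would then be 100% by construction.

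Fourth, the cost of Fisher alone is about 3.5 points (76.8% against 80.3% at 135 per group), which is small beside the uncertainty in the assumed odds ratio. That is fair as to size, but the stated 80% at 134 is still not the power of the planned test.

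A reader might infer that the 134 is an arithmetic mistake, or that the trial cannot reach 80% power on its own assumptions. The documents support neither: the 134 is exact for its formula, and one reading of the assumptions gives 81.4%.

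**Conclusion.** The point holds as a mismatch between the sample size statement and the planned analysis. Without condition, 134 per group does not give 80% power with the two-sided Fisher's test: it gives 76.7%, and 147 evaluable are needed. If the assumed rates describe completers, and with 10% dropout in both arms, power at 150 enrolled per group is 76.8% with dropouts left out and 72.1% with dropouts counted as not abstinent. The latter is what the endpoint definition and denominator imply. If the rates already count losses as failures, power is 81.4% and the shortfall disappears, but the dropout inflation is then unnecessary. The documents do not settle which reading was meant, so 72% should not be reported as the trial's power without its condition.

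**What to change.** In the Sample size section:

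1. State whether 50% and 66.7% are rates among completers or among all randomised participants.
2. Name the test used for the calculation, and state how participants lost to follow-up count in the primary rate.
3. Restate power at 150 per group for Fisher's test on all randomised participants: 72% if the rates are among completers with 10% loss in both arms, or 81% if they already count losses as failures. In the second case, drop the dropout inflation from the justification.

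This costs a few sentences, possibly a less favourable power figure, and no additional participants.

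Optionally, and only before outcomes are compared between arms, the logistic regression already named in Items analyzed and analytical methods could become the primary test. It would be adjusted for the minimization factors (age, sex, cigarettes per day, FTND score and SDS score), with Fisher's test kept as a sensitivity analysis. The trial is open-label and was recruiting when the article was submitted, so the timing and reason for such a change should be documented. The power of the adjusted model has not been calculated. The 76% above is for an unadjusted chi-square test at 45% v 60% and should not be quoted as the power of the adjusted model.
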